**Methods:**

A parallel, assessor-blinded, pragmatic randomized controlled trial with embedded cost and qualitative analysis will be completed. In total, 116 cancer survivors will be recruited from a metropolitan health network in Melbourne, Victoria, Australia. The experimental group will attend an 8-week, twice-weekly, 60-minute exercise group session supervised via videoconferencing supplemented by a web-based home exercise program and information portal. The comparison group will receive usual care including standardized exercise advice and written information. Assessments will be completed at weeks 0 (baseline), 9 (post intervention), and 26 (follow-up). The primary outcome will be health-related quality of life measured using the European Organisation for Research and Treatment of Cancer Quality of Life Questionnaire at week 9. Secondary measures include walking capacity (6-minute walk test), physical activity (activPAL accelerometer), self-efficacy (Health Action Process Approach Questionnaire), and adverse events. Health service data including hospital length of stay, hospital readmissions, and emergency department presentations will be recorded. Semistructured interviews will be completed within an interpretive description framework to explore the patient experience. The primary outcome will be analyzed using linear mixed effects models. A cost-effectiveness analysis will also be performed.

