Current telehealth approaches to exercise rehabilitation are limited in their ability to replicate traditional cancer rehabilitation. To date, no trials have evaluated the effectiveness of web-based group exercise for people with cancer [15,23]. Group exercise interventions may be superior to other exercise interventions [25] and are the most common way to deliver cancer rehabilitation in health services [3]. Groups provide a positive environment for exercise for cancer survivors [7] and allow opportunities for peer support, modeling, and feedback [26]. Groups are also an efficient way to deliver exercise that may facilitate access and be less resource-intensive on health services. There is potential for exercise groups to be delivered via telehealth as videoconferencing technology can enable the supervision of multiple participants. Since the COVID-19 pandemic, there has been a surge in the use of telehealth such as for the provision of group exercise [16,27]. Therefore, robust trials of group telerehabilitation including exercise for cancer survivors are required to determine their efficacy and effectiveness.

The primary aim of this pragmatic randomized controlled trial is to evaluate the efficacy of an exercise-based telerehabilitation program compared to usual care for improving the quality of life of cancer survivors. Secondary aims are to compare the effects of cancer telerehabilitation on walking capacity, physical activity levels, self-efficacy, and adverse events. We will also determine the costs associated with telerehabilitation and explore, in depth, the experience of cancer survivors completing cancer telerehabilitation.

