Adverse events as defined by the World Health Organization [35] will be recorded from medical records, direct observation during classes, and by participant self-report to document the safety of the intervention. The event may or may not be related to the intervention but occurs while the person is participating in the intervention phase of the trial. Adverse events will be categorized as either minor or serious and as related or unrelated and expected or unexpected events. A minor adverse event is defined as an incident that occurs while a person is participating in the intervention that results in no injury or minor injury (eg, exacerbation of pre-existing musculoskeletal pain) that requires no or minor medical intervention. A serious adverse event is defined as an incident that occurs while a person is participating in the intervention that results in death, serious injury, or hospitalization (eg, injurious fall resulting in fracture). Serious adverse events will also be recorded for the usual care group. In addition, adverse events will be reported and graded using the Common Terminology Criteria for Adverse Events Version 4 [36]. The consequences of a serious adverse event in the control group (eg, hospitalization and emergency department admission) will be captured by our health service utilization questionnaire and medical record audit. Reasons for nonparticipation in an exercise session or noncompletion of the program will be recorded (eg, pain, fatigue, and unwell).

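### Adverse events are to be compared between arms, but the event window is given in two conflicting ways and no provision is stated for recording minor events in usual care

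*Protocol article*

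**What the plan says.** The last paragraph of the Introduction states the comparison: "Secondary aims are to compare the effects of cancer telerehabilitation on walking capacity, physical activity levels, self-efficacy, and adverse events". The Abstract agrees, listing among the secondary measures "self-efficacy (Health Action Process Approach Questionnaire), and adverse events". Table 2 (primary and secondary outcomes) has no adverse-event row.

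The collection rules are in the paragraph after Table 2, under Study Outcomes:

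- Sources: adverse events "will be recorded from medical records, direct observation during classes, and by participant self-report to document the safety of the intervention".
- General window: an event counts, whether or not it is related to the intervention, if it "occurs while the person is participating in the intervention phase of the trial".
- Minor events: "A minor adverse event is defined as an incident that occurs while a person is participating in the intervention", with no injury or a minor one.
- Serious events: "A serious adverse event is defined as an incident that occurs while a person is participating in the intervention", with death, serious injury or hospitalization as the result.
- Usual care: "Serious adverse events will also be recorded for the usual care group". The consequences of such events in controls are to be picked up by the utilization questionnaire and an audit of medical records.

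The paragraph also classifies events as related or unrelated and as expected or unexpected, and applies CTCAE grading. Neither is limited to one arm.

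**The concern.** A between-group comparison of harms needs the same definition, window and sources in both arms. Here the wider window (a phase of the trial) could cover everyone. The two definitions that follow tie an event to taking part in the intervention, which a usual-care participant does not do. Staff cannot apply both rules. Only serious events are then carried over to usual care, so a site following the text has no instruction to record a minor event in a control.

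Participants are on cancer treatment or within 12 months of completing adjuvant therapy, and unrelated events count, so some background events can be expected in both arms. If they are recorded mainly in the arm seen twice a week, a safe program could look less safe than usual care. Analysis cannot repair this later, because events not recorded at the time are hard to recover.

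**Working it through.** **The document's own figures.** No adverse-event rate or adverse-event test is printed. The only related figures are the sample size, and they reproduce. With a 10-point difference, SD 18, two-sided 0.05 and power 0.80, the normal approximation gives n per arm = 2 × (1.96 + 0.842)² × (18/10)² = 50.9, so 51 per arm and 102 in total. The t-test version gives 103.7, so 104. Then 104/0.9 = 115.6, so 116. The point below does not depend on these figures.

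**The rules side by side.**

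| Feature | Telerehabilitation | Usual care |
|---|---|---|
| Trial-phase window | applies | can be read as applying |
| Participation-based definitions | can be met | cannot be met if read literally |
| Minor events | recorded | no provision stated |
| Serious events | recorded | recorded, by a separate sentence |
| Class observation | 2 × 8 = 16 sessions | none |
| Self-report | yes | no arm limit stated |
| Medical records | yes | yes |
| Utilization questionnaire (weeks 0 and 26) | yes | yes |
| Emergency and readmission data | yes | yes |

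Three things follow:

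1. The two windows conflict.
2. The serious-event definition, taken literally, excludes the controls to whom the next provision extends it.
3. Minor events have no stated route in usual care, while the other arm has 16 occasions of direct observation.

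The last three rows are common to both arms, so the asymmetry for serious events is only partial.

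**Illustration for minor events (assumptions, not trial data).** Assume 116/2 = 58 per arm (no allocation ratio is printed), the same true risk of at least one minor event in both arms, and no minor events recorded in controls.

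- At an assumed 20% risk, 0.20 × 58 = 11.6, about 12. Fisher two-sided p for 12/58 versus 0/58 = 2 × C(58,12)/C(116,12) = 0.00026.
- With zero recorded in controls, 5 events in the other arm give p = 2 × C(58,5)/C(116,5) = 0.057, and 6 give 2 × C(58,6)/C(116,6) = 0.027. Six are therefore enough for p < 0.05.
- The chance of a false difference at 0.05 is 0.53 at 10% risk, 0.98 at 20% and above 0.999 at 30–40%. With equal recording it is 0.02–0.03.

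**Illustration for serious events.** If controls captured a fraction s of equally frequent events, the apparent risk ratio would be 1/s: 1.33 at s = 0.75 and 2.0 at s = 0.50. For assumed risks of 10–30%, the chance of a false difference is 0.03–0.11 and 0.08–0.41 respectively. The document gives no reason to expect a particular s, and the shared hospital sources argue for a value nearer 1.

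**The case against.** The strongest reply is that the paragraph already contains a usable rule. The trial-phase window can be read as covering both arms, records and self-report carry no arm limit, serious events are expressly extended to controls, and no sentence excludes minor events in usual care. The stated purpose of collection is to document the safety of the intervention, and no hypothesis test for adverse events is printed. The schedule of assessments is in an appendix that is not shown, so a common week-9 question may exist.

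Much of this stands, and it rules out several stronger readings:

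- A reader might infer that a control can never have an adverse event. The trial-phase sentence and the usual-care sentence say otherwise.
- A reader might infer that source, intensity and window all differ by arm for serious events. The questionnaire and audit are said to capture the consequences of control events, not to be the only way of finding them. The hospital sources serve both arms.
- A reader might infer that treatment symptoms will be counted as harm from the program. Classification as related or unrelated limits that, and a minor event is worded as an incident, which need not include background symptoms.

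The reply does not remove the conflict between the two windows. Nor does it supply a provision for minor events in usual care, and the Introduction still commits the trial to a comparison.

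**Conclusion.** The point holds in a limited form. The stated comparison does not match the collection rules. As written, a comparison of minor events, or of totals that include them, would partly measure surveillance, and the serious-event definition contradicts its extension to usual care.

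It would go too far to say that the adverse-event aim cannot be answered. Serious events can be compared from the shared sources, and emergency and hospital admissions have their own planned analysis by negative binomial regression. The effect is confined to a secondary safety comparison. The primary outcome and the sample size of 104 (116 randomized) are untouched.

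The size of the bias cannot be derived from the document. The 12/58 versus 0/58 example rests on an assumed 20% risk, an assumed 58 per arm, no recording at all in controls, and a test the article does not plan. It shows how such a bias would act, not what this trial will find.

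**What to change.** - Define minor and serious events by one calendar window, randomization to week 9, for every randomized participant, and remove the wording that ties them to participation in the intervention.
- Ask both arms the same adverse-event question at the existing week-9 assessment. Word it without reference to classes, since the assessor is blind to allocation.
- Apply the same record audit and CTCAE grading to both arms, with event dates so that the window can be enforced.
- Base the between-group comparison only on these common sources, and report class-observed events descriptively for the telerehabilitation arm.
- If minor events will not be collected alike, restrict the aim in the Introduction to serious events and describe minor events for one arm only.

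The cost is a wording change, a few extra questions at a visit that already takes place, and more background events on record. Fourteen participants were enrolled by June 2022. Any who passed week 9 before the change would lack the common question, and the report should say so.

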### Consumer Perceptions

Semistructured interviews will be completed on 2 occasions (immediately after the intervention at week 9 and at week 26) with experimental group participants to explore in detail the experience of people participating in exercise-based cancer telerehabilitation and of behavior change. A purposive sample of participants in the telerehabilitation group will be asked questions relating to satisfaction, barriers, and facilitators to accessing cancer telerehabilitation and perceptions about sustaining physical activity on program completion. The same group will be interviewed at both time points. We will conduct interviews until we reach data saturation; that is, until no new ideas emerge from the data [37]. It is anticipated that this will be achieved by interviewing approximately 20 participants based on our previous qualitative studies of cancer rehabilitation [7,11]. Interviews of approximately 45-minute duration will be conducted in person, via the telephone, or through videoconference, if preferred, by a member of the research team. A different interview schedule at each time point (Multimedia Appendix 4) will be given to participants prior to the interview to allow them to prepare.

Other routinely collected data will be used to describe the sample, including age, gender, cancer type, cancer stage, treatment regimens, comorbidities, baseline functional performance status (AKPS), and baseline BMI.

### Sample Size Estimation

It is estimated that 104 participants will be required to accomplish a power of 0.80 and a 2-tailed α level of .05 to detect a between-group difference of a 10-point change in the EORTC QLQ-C30 score [38] (the minimally important difference established for cancer survivors) assuming an SD of 18 points [39]. Based on our previous trial of cancer rehabilitation [39], we expect a dropout of 10%; therefore, 116 participants will be randomized.

### Statistical Analysis

#### Analysis of Quantitative Data

The primary outcome (postintervention global health–related quality of life) will be analyzed using linear mixed effects models. Modeling will account for variation in baseline values. This method accounts for within-participant dependence of observations over time, and for missing data, allowing some participants to have missing observations at certain time points. If more than 5% of data are missing, a multiple imputation process will be used, providing the assumption that data are missing at random is met. A similar approach will be used for analysis of secondary continuous outcomes collected longitudinally. The time spent in moderate to vigorous physical activity will be estimated using a cut-off of 100 steps per minute for moderate-intensity physical activity [40]. The proportion of participants meeting physical activity guidelines will be described and compared using risk ratios. The number of emergency department and hospital admissions will be reported as an incidence rate ratio using a negative binomial regression model. To avoid bias and to maximize the randomization process, all available data will be analyzed in accordance with allocation (intention-to-treat analysis) regardless of adherence.

Total direct costs to the health service for each participant will be determined from the intervention costs and cost of health services utilized over 6 months as recorded from hospital administrative data and health service utilization questionnaire. Costs associated with delivering telerehabilitation will be attributed to the experimental group and cost associated with usual care will be attributed to the comparison group. These will be determined from a register of staff and the time engaged in telerehabilitation or usual care for each participant. Labor costs will be attributed to the staff member and the cost of the telerehabilitation intervention and usual care (based on time and location) to determine a total intervention cost for each participant as well as infrastructure costs. Total costs for each participant will be determined from the intervention costs, the cost of health services utilized over 6 months for experimental group participants, and the cost of health services utilized over 6 months for comparison group participants. The incremental cost-effectiveness ratio will be calculated as the difference in total program and health service costs per mean difference in the global quality-of-life score between the comparison and experimental groups over 6 months. A cost utility ratio will be calculated on the basis of the EORTC-QLQ C30 global quality-of-life score [41] as the change in total program and health service cost per change in quality-adjusted life years saved in the experimental and comparison groups over 6 months.

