### Randomization Procedures

Eligible participants who have completed baseline measurements will be randomly allocated to the telerehabilitation group or usual care control group using a concealed method in accordance with a web-based computer-generated randomization program using permuted blocks of 4, 6, and 8 participants. Allocations will be prepared prior to trial commencement by an independent researcher with no role in participant recruitment, trial administration of intervention delivery, or assessments. The trial coordinator will allocate participants after baseline assessment by contacting the independent researcher via email for random group allocation.

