### Inclusion and Exclusion Criteria

Participants will be eligible if they are aged 18 years and over, have a cancer diagnosis and are receiving cancer treatment (palliative or curative intent) or are within 12 months of completing adjuvant therapy (except for long term oral hormonal therapies), are functioning independently in the community (Australian Karnofsky Performance Status [AKPS] score≥60), are at a low risk of falls (Falls Risk for Older People in the Community score<4), are able to speak conversational English so participants can engage effectively in videoconferencing, have access to and be willing to use the internet, and be able to give written informed consent.

Participants will be excluded if they are medically unfit to participate in exercise as determined by a physiotherapist or medical practitioner on the basis of published recommendations [32], are residing in residential care or are an inpatient, or have cognitive impairment precluding the ability to provide written informed consent as assessed by their treating clinician.

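### Optional gain: the primary model names only baseline values for adjustment, so treatment intent or phase and AKPS could be added for a little precision at almost no cost

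*Protocol article*

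**What the plan says.** All places are in the protocol article.

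- **Analysis of Quantitative Data:** week-9 global quality of life is analysed with a linear mixed effects model. The only words on covariates are "Modeling will account for variation in baseline values". A similar approach is announced for the continuous longitudinal secondary outcomes.
- **Randomization Procedures:** allocation is made "using permuted blocks of 4, 6, and 8 participants". No stratification factor is named.
- **Inclusion and Exclusion Criteria:** patients qualify if they are "receiving cancer treatment (palliative or curative intent) or are within 12 months of completing adjuvant therapy", with an AKPS score of at least 60.
- **Consumer Perceptions (last paragraph):** routinely collected data, among them "cancer type, cancer stage, treatment regimens, comorbidities, baseline functional performance status (AKPS"), are given one use, which is to describe the sample.
- **Sample Size Estimation:** "104 participants will be required to accomplish a power of 0.80 and a 2-tailed α level of .05". The target difference is 10 points on the EORTC QLQ-C30, and the planning SD is 18 points. For attrition: "we expect a dropout of 10%; therefore, 116 participants will be randomized". No credit is taken for covariate adjustment.

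**The concern.** The eligibility criteria deliberately mix patients who differ in treatment intent and in phase of treatment. Two patients with the same week-0 score, one on palliative treatment and one some months past adjuvant therapy, may have different expected scores at week 9. Adjusting for baseline removes differences in starting level. It need not remove differences in expected course.

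Neither the randomisation nor the stated model refers to intent, phase or performance status. The trial records AKPS and treatment regimens, and it must establish intent and phase to apply its eligibility criteria. If these variables predict week-9 quality of life beyond the baseline score, leaving them out makes the confidence interval somewhat wider than it needs to be. An imbalance noticed after unblinding could also invite post hoc adjustment, which is less convincing than a rule fixed in advance.

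**Working it through.** **1. The plan's own figure.** Inputs from Sample Size Estimation: difference 10, SD 18, two-sided alpha 0.05, power 0.80, dropout 10%. A 1:1 ratio is assumed, as none is stated.

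- Two-sample t-test (noncentral t): 52 per arm, 104 in total, power 0.801. This matches the stated 104. The normal approximation gives 51 per arm.
- Dropout: 104/(1 - 0.10) = 115.6, rounded up to 116. This matches.

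The power target is therefore met with no covariate at all.

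**2. How large chance imbalance could be.** The article gives neither the palliative share nor the difference in course, so both are assumptions. With 58 randomised per arm and share p, the SD of the arm difference in share is sqrt(p(1 - p) × 2/58).

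| Assumed share | SD of arm difference | Chance of a gap of 10 percentage points or more |
|---|---|---|
| 20% | 0.074 | 18% |
| 30% | 0.085 | 24% |
| 50% | 0.093 | 28% |

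At a 30% share, the resulting shift in the estimated effect depends on the assumed difference in course d. The SD of the shift is 0.085 × d, and the 95% limit is 1.96 times that.

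| Assumed d (points) | SD of shift | 95% limit | Share of planning variance, 0.3 × 0.7 × d²/18² |
|---|---|---|---|
| 5 | 0.43 | 0.8 | 1.6% |
| 10 | 0.85 | 1.7 | 6.5% |
| 15 | 1.28 | 2.5 | 14.6% |

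Imbalance and lost precision are one effect. For d = 10, the variance of the shift is 0.85² = 0.72. The variance of the unadjusted difference is 18² × 2/58 = 11.17. The ratio is 6.5%, the same as in the last column.

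**3. What adjustment would gain.** Let r be the share of the variance remaining after baseline adjustment that the added covariates explain. An assumed r of 5-10% is consistent with step 2.

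- The standard error is multiplied by sqrt(1 - r): 0.975 at 5% and 0.949 at 10%, a fall of about 2.5% and 5%.
- Residual SD = 18 × sqrt((1 - R²) × (1 - r)), where R² is the share already explained by baseline quality of life. Power is at 52 per arm (noncentral t, 98 degrees of freedom).

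| Assumed baseline R² | Residual SD at r = 0 | Power, r = 0 | r = 5% | r = 10% |
|---|---|---|---|---|
| 0 (18 is already the SD after baseline adjustment) | 18.00 | 0.801 | 0.821 | 0.841 |
| 0.25 | 15.59 | 0.900 | 0.914 | 0.927 |
| 0.36 | 14.40 | 0.939 | 0.949 | 0.959 |

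The first row gains 2-4 percentage points and the other two gain 1-3. The article does not say which kind of SD the 18 is, so the rows cannot be narrowed.

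**The case against.** **Silence in a condensed article.** The sentence on baseline values does not say that no other covariate will be used, nor that only the baseline of the outcome is meant. A covariate list is commonly left to the analysis plan, which is not shown. This stands: the absence of a list is no defect, and the suggestion is conditional on what that plan says. What remains is that the article does state a use for the recorded characteristics, and that use is descriptive.

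**Nothing is invalid.** A reader might infer that a chance imbalance in the palliative share biases the week-9 comparison. It does not. Under random allocation, such imbalance adds variance, and the standard error already reflects it. No stratification factor is named, so the model omits no known design factor.

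**Missing data.** A reader might also infer that omitting these variables undermines the missing-at-random assumption. That would require dropout to depend on them given what is already in the model. The article gives only a 10% dropout rate and nothing on its causes, so this cannot be claimed.

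**The prognostic premise is assumed.** The documents give no palliative share, difference in course or correlation. Eligibility also narrows the mix: AKPS of at least 60, low falls risk, no inpatients, fit to exercise. Baseline quality of life may already carry part of the difference between patient groups. All of this stands, and it is why the gain is given as a range.

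**Data availability.** Intent and phase are not in the list of recorded characteristics. They would have to be derived from the eligibility assessment and the treatment regimen data, which is a small task but not zero.

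**Conclusion.** This is an optional improvement, not an error. The stated analysis is valid and unbiased, and 104 and 116 are correct for the stated inputs. Some precision may be left unused: a standard error about 2.5-5% larger than it need be, worth 2-4 percentage points of power from 0.80, or 1-3 points from 0.90-0.94 if baseline quality of life already explains much of the variance. These figures rest on the assumed 5-10% of remaining variance, the assumed baseline R² of 0, 0.25 or 0.36, and 1:1 allocation.

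The stronger reading, that the trial is underpowered or its result distorted without these covariates, is not supported. The planned power is reached without them. Even an imbalance at the 95% limit, with an assumed 30% palliative share and a 10-point difference in course, moves the estimate by 1.7 points. The typical (SD) shift is 0.85, against an unadjusted standard error of 18 × sqrt(2/52) = 3.53.

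**What to change.** First check whether the analysis plan already lists these covariates. If it does, nothing is needed.

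Otherwise, before unblinding, add one sentence. It should say that the primary model and the models for continuous secondary outcomes include, alongside the baseline value of the outcome, fixed effects for baseline AKPS and for treatment status and intent. The latter has three levels: on curative treatment, on palliative treatment, and completed adjuvant therapy within 12 months. State how these levels are derived from the eligibility and treatment regimen data. If the model treats the week-0 score as a response and not as a covariate, let these terms vary by visit, because a main effect alone would adjust level and not course.

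With baseline as a covariate, the cost is about 3 degrees of freedom (two for the three-level factor, one for AKPS as a linear term), plus the work of deriving one variable. Randomisation and sample size do not change.

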Physiotherapists conducting assessments and providing the exercise intervention will be trained in exercise rehabilitation for cancer survivors. They will participate in a 1-day web-based training session about cancer care and complete a self-directed web-based module about cancer-related fatigue management. They will also participate in 2 interactive 2-hour in-person workshops about exercise prescription for cancer survivors. They will also have access to a website [33] that provides education for clinicians providing exercise-based cancer rehabilitation. Physiotherapists will receive monthly clinical supervision in line with health service policy and regular mentoring with senior research staff. The fidelity of the intervention will be monitored by recording the content of exercise sessions using logbooks, including the number and duration of completed sessions. Participants in both groups will also be asked whether they received any exercise-based intervention outside of the trial at the 9-week assessment and 4-month follow-up.

**Table 1 table1:** Intervention and comparison group descriptions using the template for description and replication checklist (TIDier).

			Experimental group		Comparison group
Brief name			Group exercise–based cancer telerehabilitation		Usual care
Why			Exercise interventions delivered via telehealth can be safe and effective for improving the quality of life of cancer survivors and offer convenience		Cancer survivors are not routinely offered cancer rehabilitation
What: materials			2× weekly web-based supervised, group-based exercise (approximately 6 participants per group; Zoom) Participants will be provided with an exercise band Participants to receive a web-based (Physitrack), individualized home exercise program, and exercise band Participants to receive access to a web-based information portal (iLearn) with webinars, web-based information handouts, and resources about cancer care and recovery including exercise Participants will wear a physical activity device (Fitbit Inspire) continuously during waking hours for 8 weeks Written information about local exercise services provided at 8 weeks		Standard information booklets about cancer care and recovery including exercise Written information about local exercise services provided at 8 weeks

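### Group delivery in one arm: neither the sample size nor the primary model as described allows for clustering by exercise class

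*Protocol article*

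**What the plan says.** Table 1 of the Protocol article describes the experimental treatment as "group-based exercise (approximately 6 participants per group; Zoom". The intervention section sets two supervised 60-minute sessions a week for 8 weeks. Table 1 lists one physiotherapist and one allied health assistant for the group sessions. The comparison arm receives advice, written material and usual care, with no classes. The Introduction says that groups "allow opportunities for peer support, modeling, and feedback".

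Under Sample Size Estimation, "104 participants will be required to accomplish a power of 0.80" at a two-tailed α of .05, to "detect a between-group difference of a 10-point change in the EORTC QLQ-C30 score", "assuming an SD of 18 points". The only inflation is for attrition: "we expect a dropout of 10%; therefore, 116 participants will be randomized".

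Under Analysis of Quantitative Data, the primary outcome is analysed with linear mixed effects models that take account of baseline values. The one form of dependence described is the repeated measurement of a participant: "This method accounts for within-participant dependence of observations over time, and for missing data". Continuous secondary outcomes measured longitudinally are to be handled in a similar way.

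**The concern.** Patients who share a class also share staff, session content and each other's company for 8 weeks. Part of the article's case for groups is interaction among participants, which is a reason to expect outcomes within a class to be somewhat alike. Only one arm is affected, so this is a partially nested design: clustered in the experimental arm, independent in the control arm.

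If class means differ by more than chance, the experimental-arm mean is less precise than 52 independent patients would make it. A model without a class term then reports a primary confidence interval that is too narrow and a test that rejects too often. A test that does allow for classes has less power than an independence calculation at the same sample size.

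**Working it through.** **Inputs from the Protocol article.** Difference 10, SD 18, two-sided α 0.05, power 0.80, 104 evaluable and 116 randomized (Sample Size Estimation); class size about 6 (Table 1).

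**Assumed.** 1:1 allocation, so 52 evaluable per arm (two arms, even block sizes; the ratio is not stated). ICC of 0.02, 0.05 or 0.10 (none is given).

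**Reproducing the stated figure.** A two-sample t-test with 52 per arm, difference 10 and SD 18 has power 0.801; 51 per arm gives 0.793. So 2 × 52 = 104, and 104/0.9 = 115.6, rounded up to 116. The figure reproduces with no allowance for clustering and no credit for baseline adjustment.

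**Adding the classes.** With m = 6, the design effect in the experimental arm alone is DE = 1 + (m − 1) × ICC. Then:

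- Standard error under independence: 18 × √(1/52 + 1/52) = 3.53.
- Standard error with classes: 18 × √(DE/52 + 1/52).
- Two-sided type I error of a test that ignores classes: 2 × [1 − Φ(1.96 × 3.53/SE)].
- Power by the normal approximation: Φ(10/SE − 1.96).

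| ICC | DE | SE | SE relative to 3.53 | Type I error, classes ignored | Power, normal approximation | Power, about 9 closed classes |
|---|---|---|---|---|---|---|
| 0 | 1.00 | 3.53 | 1.000 | 0.050 | 0.81 | 0.78 |
| 0.02 | 1.10 | 3.62 | 1.025 | 0.056 | 0.79 | 0.76 |
| 0.05 | 1.25 | 3.74 | 1.061 | 0.065 | 0.76 | 0.73 |
| 0.10 | 1.50 | 3.95 | 1.118 | 0.080 | 0.72 | 0.68 |

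The last column uses a noncentral t distribution with 9 classes averaging 52/9 = 5.8 patients and Satterthwaite degrees of freedom of about 21 to 28. Its ICC 0 row shows that about 3 points of the difference from the normal approximation come from estimating a variance with few classes, not from clustering. A simulation with 9 classes agrees: power about 0.76, 0.73 and 0.68, and type I error with classes ignored of about 0.054, 0.064 and 0.077.

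**Effect of baseline adjustment.** Suppose that 18 is an unadjusted SD, which the article does not say, and that the baseline correlation is r. The residual SD is then 18 × √(1 − r²), and the ICC is applied to that residual. With r = 0.3 the SD is 17.2, and power with 9 classes is about 0.80, 0.77 and 0.72 at the three ICCs. With r = 0.5 the SD is 15.6, and power is about 0.87, 0.84 and 0.80. The ratio of the true to the independence standard error depends only on DE, so adjustment leaves it unchanged at a given residual ICC.

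**The case against.** **The ICC is unknown.** A reader might infer that the standard errors are too small and that the stated power is not delivered. The documents support neither as a fact. At an ICC of 0.02 the loss is about 2 points of power by the normal approximation, and individually tailored exercise gives no reason to expect a large value. This objection stands; the point is conditional.

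**Baseline adjustment may cover the loss.** With r = 0.5, power is about 0.80 or better up to an ICC of 0.10. It would therefore be wrong to say that 104 gives 0.80 only if the ICC is zero. This also stands for power, but not for the standard error.

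**Type I error need not rise.** Randomization is individual. If the programme changes nobody's outcome, sharing a class adds no correlation and the test keeps its size. Inflation requires real class-to-class variation around a zero average effect. This stands as a limit on the claim.

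**The class structure is not described.** Nothing says that classes are closed cohorts. About 58 experimental patients (half of 116), each treated for 8 weeks, over some 19 to 20 months of recruitment (April 2022 to late 2023, about 82 to 87 weeks) means 58 × 8/87 to 58 × 8/82, or 5.3 to 5.7 patients in treatment at once. That fits a single rolling class equally well. The 9-class column is an illustration.

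**Class membership may not be logged.** The fidelity records cover session content, number and duration. One might infer that they show who shared a class, but the article does not say so.

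**The model is a condensed description.** The article does not say that participant is the only random effect, and an analysis plan that is not shown could add a class term. That softens the modelling half of the point. It does not reach the sample size, which is fixed in the article and contains no allowance for clustering.

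**Conclusion.** The point holds in conditional form. The experimental arm is treated in shared classes of about 6, and neither the stated sample size nor the model as described allows for it. If outcomes vary between classes, the true standard error exceeds the independence one by about 2.5%, 6% and 12% at ICCs of 0.02, 0.05 and 0.10, and type I error is about 5.6%, 6.5% and 8.0%. Power at 104 evaluable, before baseline adjustment, is about 0.79, 0.76 and 0.72, or about 0.76, 0.73 and 0.68 under the 9-closed-class illustration. The shortfall becomes material from an ICC of about 0.05.

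These figures rest on assumed ICCs, 52 evaluable per arm and classes of 6. Baseline adjustment may offset some or all of the power loss but cannot repair the standard error. This should be fixed before outcome data are seen. Confidence is medium, because the ICC, the class structure and the full analysis plan are not available.

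**What to change.** - **Model.** Prespecify a partially nested mixed model: a class random effect in the experimental arm only, arm-specific residual variances, and Satterthwaite or Kenward-Roger degrees of freedom. Carry the same term into the continuous secondary outcomes, which are to be analysed similarly.
- **Class definition.** Record a class for each experimental participant, assigned at allocation, so that patients who never attend stay in the intention-to-treat analysis. If membership rolls, use a time-block or multiple-membership term.
- **Sample-size paragraph.** State that 0.80 assumes no class clustering and no gain from baseline adjustment. Show power over a stated ICC range, with any assumed baseline correlation, and say whether the SD of 18 refers to raw or change scores.

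**Cost.** No extra patients and no change to treatment. The price is a slightly wider interval, an imprecisely estimated class variance if classes are few, and the work of logging class membership.
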